### Patient and public involvement

The PREDMEN trial is supported by the Dutch Association for the hard of hearing, and more specifically, its Committee Dizziness and Balance (Commissie Duizeligheid en Evenwicht van Hoormij-NVVS) and the Dutch association for psychological healthcare and social services for patients with SNHL and tinnitus (GGMD). Both organisations are involved in the realisation of the trial, the writing process and implementation of trial results. Moreover, they will serve as a sounding board for MD patients participating in this trial and one patient representative will be a member of the steering committee. In line with their suggestions, patients will be involved in every stage of the research.

## Ethics and dissemination

### Ethics

The PREDMEN trial was submitted via the Clinical Trial Information System (CTIS), with CTIS number: *2023-503340-13-00*, reviewed by the Medical Research Ethics Committee Leiden The Hague Delft (MREC LDD), and authorised for execution in the Netherlands under the European Clinical Trial Regulation (ECTR). Additionally, the institutional research board and the Board of Directors of each participating centre (Franciscus Gasthuis & Vlietland, Gelre ziekenhuizen, HagaZiekenhuis, Leiden University Medical Centre, Maastricht University Medical Centre, Medisch Spectrum Twente) individually reviewed and approved the study. The study is conducted in accordance with the principles outlined in the Declaration of Helsinki (October 2013), the Medical Research Involving Human Subjects Act (WMO, 26 February 1998), the International Conference on Harmonisation Good Clinical Practice (ICH GCP, November 2016) guidelines, and any other applicable guidelines, regulations and Acts.

### Patient safety

Minor complications such as persistent membrane perforation (5.9%) and otitis media (7%) can occur.^7 28 29^ Safety risk will be comparable to normal clinical practice and it is not expected that significant adverse events will be seen in the intervention arm. ENT specialists are experienced with intratympanic injections due to its application in patients with sudden deafness. Since the intervention is characterised as a low risk profile study, no Data Safety Monitoring Board (DSMB) is required.^30^ The sponsor will submit a report on the safety of each investigational medicinal product used in the clinical trial through CTIS. Interim analysis will be performed on the primary endpoint when 50% of the patients have been randomised and completed a follow-up of 6 months, where comparability of baseline characteristics will be assessed. In these analyses, differences in vertigo control between the two study arms should not be greater than 45%. In addition, if the difference in vertigo control reveals to be clinically significant (ie, >20%), but ≤20% of the participants in methylprednisolone reach vertigo control, the study will be terminated because of convincing effect of the treatment in the intervention arm.

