### Sample size

A sample size calculation was performed based on recommendations as summarised in the Clinical Practice Guideline for Menière’s disease.^1^ An expected proportion of subjects achieving vertigo control of 87.5% was assumed for methylprednisolone treatment compared with an assumed 67.5% for placebo, that is, a difference in treatment effect of 20%. With a statistical power (1-β) of 80% and a type 1 error (α) of 5%, 67 patients per group are required. With an estimated 10% loss-to-follow-up, 74 patients will be included in each arm, giving a total sample size of 148. In total, over the six participating centres, 340 MD patients yearly visit the Otolaryngology department and will be screened for the trial. It is expected that 15% will meet the inclusion criteria and will be willing to participate. This will result in approximately 50 eligible patients for inclusion per year.

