### Randomisation and blinding

Subjects will be randomly assigned to either methylprednisolone or placebo with a 1:1 allocation as per computer-generated random sequence, stratified by site generated by Castor EDC. Blinding will be maintained until all subjects have finished their treatment phases. All study participants, participating medical professionals and outcome assessors will be blinded. The independent epidemiologist and pharmacy personnel will both be unblinded during randomisation and therapy allocation.

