### Statistical analysis

Ordinal regression using mixed model analysis will be used to analyse the primary outcome (ie, class of vertigo). In addition, generalised estimating equation analysis of the actual vertigo attacks recorded using the DizzyQuest app will be used to estimate the incidence rate ratio for comparison between the methylprednisolone and placebo groups. A decrease of 100% is considered total control of vertigo episodes, while a reduction of >40% is considered a substantial and thus clinically relevant reduction.^17^

Mixed model analysis will be used to analyse differences in the questionnaire scores (DHI, TFI, FLS, eQ-5D/VAS, iMCQ, iPCQ) between the two groups. Logistic regression analysis will be used to analyse the remaining secondary outcomes (incidence of escape interventions, hearing loss and adverse events). A reduction in hearing of 10 decibels or a 15% change in word recognition will be regarded as a clinically significant difference.^17^

Subgroup analyses will be performed with regard to sex, duration of the disease and the type of MD (delayed MD, familial MD and autoimmune MD). These subgroups will be defined as described in Frejo *et al*.^25^ Two sensitivity analyses will be carried out in addition to the intention to treat analysis: a per protocol analysis in which patients who received additional co-interventions to achieve vertigo control are excluded; and an as-treated analysis in which participants who received additional co-interventions are analysed.

In order to evaluate the average costs and outcomes between the methylprednisolone and placebo groups for the cost-effectiveness analysis, intention-to-treat and net-benefit analysis will be used. For all statistical analysis, multiple imputation to adjust for missing data will all be used.^26^ QALYs will be calculated using the Dutch tariff for the EuroQoL EQ-5D-5L^23^ and as sensitivity analysis, the visual analogue scale valuing health, with power-transformation.^27^ All outcomes with corresponding statistical analysis methods are summarised in table 2. A p value <0.05 will be considered as statistically significant for all analyses and will be performed using SPSS V.25 or higher (SPSS Chicago Illinois, USA).

**Table 2 T2:** Outcomes with corresponding statistical analysis method

	Outcome	Type of data	Analysis
Primary outcome	Number of spontaneous vertigo attacks, lasting more than 20 min	Count	Generalised estimating equation

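### The protocol plans an interim stop for benefit but allots no alpha to it; the printed rule cannot fire for methylprednisolone, and any workable version would raise the type 1 error to about 7% to 9%

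*Protocol article*

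**What the plan says.** Four statements in the protocol article bear on this.

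- **Patient safety, timing and endpoint:** "Interim analysis will be performed on the primary endpoint when 50% of the patients have been randomised and completed a follow-up of 6 months".
- **Patient safety, limits:** the between-arm difference in vertigo control should stay within 45%, with no consequence given. If the difference exceeds 20% but no more than 20% of the methylprednisolone arm reach control, "the study will be terminated because of convincing effect of the treatment in the intervention arm".
- **Statistical analysis:** "A p value <0.05 will be considered as statistically significant for all analyses".
- **Sample size:** "With a statistical power (1-β) of 80% and a type 1 error (α) of 5%, 67 patients per group are required".

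The interim limits are thresholds on observed differences. The article gives no interim p value, no spending of alpha and no reduced final level.

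**The concern.** A between-arm look at the primary endpoint that can end the trial for benefit is a second chance to declare success. If the final test keeps the whole 5%, the two chances together exceed 5%. The article commits to the efficacy stop, to a trigger on the raw difference and to an unadjusted 0.05, so this is more than detail deferred to the analysis plan. A boundary added later would have to override this text.

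Two things are at stake. A phase 3 trial could declare methylprednisolone effective more often than its stated error rate allows. A trial stopped at half its size because the observed gap passed 20 points would also tend to report an exaggerated effect.

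**Working it through.** **Inputs.** Control rates of 87.5% and 67.5%, α 5%, power 80%, 67 per group, 10% loss, 74 per arm and 148 in total (Sample size); 1:1 allocation (Randomisation and blinding); interim at 50% (Patient safety). Half of 148 is 74 patients, or 37 per arm, so the information fraction is about 0.5.

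**1. The plan's own figure.** With a two-sided 5% test and pooled variance under the null:

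n = [1.960·√(2·0.775·0.225) + 0.842·√(0.875·0.125 + 0.675·0.325)]² / 0.20² = (1.157 + 0.483)² / 0.04 ≈ 67.2.

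This agrees with the stated 67 (68 if rounded up; the unpooled formula gives 64.5; a one-sided test would need 53). Then 67 × 1.10 = 73.7, giving 74. The sample size therefore belongs to a single two-sided test at the full 5%.

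**2. The rule as printed.** Let m and c be the observed control rates on methylprednisolone and placebo. A stop in favour of methylprednisolone needs m − c > 0.20 and m ≤ 0.20, hence c < 0, which is impossible. Taking the difference in either direction, the rule fired in none of the simulated trials at the planned rates, so the overall error stays at 5.0%. At a common control rate of 30% it fires in 1.7% of trials, always with placebo ahead, and the overall error is 6.2%.

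**3. The 45-point limit.** At a common rate of 67.5% the standard error of the difference is √(2·0.675·0.325/37) = 0.109, so 45 points is z = 0.45/0.109 ≈ 4.1. It is crossed with probability about 0.00003. If it is an efficacy stop, the overall error is still 5.0%.

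**4. A stop that works as its stated reason says.** On the same standard error, 20 points is z = 0.20/0.109 ≈ 1.84, which is below 1.96. For example, 33/37 against 25/37 is a gap of 8 patients (21.6 points). The pooled rate is 58/74 = 0.784, the standard error is 0.096 and z = 2.26, so p = 0.024 (Fisher 0.046). For an 8-patient gap at any starting count, the chi-square p runs from 0.003 to 0.063.

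**5. Overall two-sided type 1 error.** Vertigo control is treated as binary with a pooled z test, a true rate of 67.5% in both arms, and at least 1,000,000 simulated trials per scenario.

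| Rule | 37 then 74 per arm | 33 then 67 per arm |
|---|---|---|
| Final test only | 5.0% | 5.1% |
| p<0.05 at both looks | 8.4% | 8.7% |
| Stop if methylprednisolone leads by >20 points, then final p<0.05 | 7.2% | 8.3% |
| Stop on >20 points either way, then final p<0.05 | 9.3% | 11.4% |

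The bivariate normal calculation with correlation √0.5 gives 8.3% for the second row. If the interim and final results correlate less than that, this row rises towards 1 − 0.95² = 9.75%. Over common rates from 15% to 87.5%, the last row runs from 5.4% to 11.4% at 37 then 74 per arm.

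**6. Under the planning effect (87.5% against 67.5%).** The working 20-point stop fires in about 49% of trials at 37 per arm. In those trials the mean observed difference is 27.7 points, against a true 20.

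**The case against.** The strongest reply is that the printed rule inflates nothing. Its 20% ceiling on methylprednisolone control blocks any stop in that arm's favour, and the 45-point limit is stricter than the usual interim boundaries. Both statements are correct. A reader might infer that the 5% error rate already fails under the text as it stands. The document does not support that, because the inflated figures belong to a reconciled rule or to an interim tested at p<0.05.

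It can also be said that the interim is a set of thresholds and not a test, and that the p<0.05 sentence closes the account of the main analyses without mentioning the interim. That is fair. Applying it to the interim is one reading of the words about all analyses, and the 8.4% depends on that reading.

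Third, the planned analyses are an ordinal mixed model and generalised estimating equations on attack counts, over 6 and 12 months. The binary calculation is an approximation, so the decimals are illustrative.

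Lastly, boundaries are often placed in an analysis plan that is not shown here. This answers only part of the point, because the article itself states both an efficacy stop and an unadjusted 0.05. Nor does the impossible clause protect the trial. The sentence says it exists to stop for benefit, so the clause will have to be corrected, and correcting it alone would activate a stop without error control.

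**Conclusion.** The point holds conditionally. The protocol plans a comparative interim with an efficacy stop on an observed difference and allots no alpha to it. At the planned rates the printed rule adds no error and the 45-point limit practically none. Once the stop is made to work as intended, or the interim is tested at p<0.05, the overall two-sided error is about 7% to 9% at a 67.5% control rate, or 8% to 11% with 33 and 67 evaluable per arm. About half of trials under the planning effect would then stop early, with the difference overstated by some 8 points on average.

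These sizes assume a two-sided test (the article gives no sidedness, but only two-sided reproduces its sample size), the same binary control measure at both looks, and half the information at the interim. The exact error cannot be fixed until the 20% and 45% clauses are reconciled.

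**What to change.** Before the interim is run:

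1. Reconcile the three clauses under Patient safety (difference above 20%, at most 20% control on methylprednisolone, difference not above 45%), and state the consequence of each.
2. Replace the observed-difference efficacy trigger with a formal boundary on one named primary test, and exempt the interim from the general p<0.05 rule. Examples, two-sided at half the information:
   - Lan-DeMets O'Brien-Fleming-type spending: interim p<0.003, final p<0.049.
   - Haybittle-Peto: interim p<0.001, final p<0.0498.
3. Alternatively, state that the interim cannot stop the trial for benefit.

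The cost is a few sentences and no extra patients. With either boundary, simulated power is essentially unchanged: 0.845 at 74 per arm, and 0.807 to 0.808 at 67. The downside is fewer early efficacy stops under the planning effect at 37 per arm: about 17% with Lan-DeMets and about 9% with Haybittle-Peto, against about 49% for a working 20-point trigger.

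### The interim stop for a convincing effect of methylprednisolone can be met only when placebo is ahead by more than 20 points

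*Protocol article*

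**What the plan says.** All of the interim rule stands in the protocol article under Patient safety.

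- Timing: "Interim analysis will be performed on the primary endpoint when 50% of the patients have been randomised and completed a follow-up of 6 months".
- First limit: "differences in vertigo control between the two study arms should not be greater than 45" per cent. No direction is given, and nothing is said about what follows if it is exceeded.
- Termination rule, first condition: "if the difference in vertigo control reveals to be clinically significant (ie, >20" per cent).
- Termination rule, second condition and consequence: "but ≤20% of the participants in methylprednisolone reach vertigo control, the study will be terminated because of convincing effect of the treatment". The treatment meant is methylprednisolone, since the sentence closes by naming the intervention arm.

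The Sample size section fixes the scale and the design rates. For the active arm: "An expected proportion of subjects achieving vertigo control of 87.5% was assumed for methylprednisolone treatment". For the control arm and the resulting difference: "compared with an assumed 67.5% for placebo, that is, a difference in treatment effect of 20" per cent. That is a subtraction of two percentages, so differences in control are in absolute points.

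The Statistical analysis section sets one threshold: "A p value <0.05 will be considered as statistically significant for all analyses". The primary analyses named there are an ordinal mixed model for class of vertigo and generalised estimating equations (GEE) for attack counts.

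**The concern.** The termination rule joins two conditions, a difference above 20 points and a methylprednisolone control rate of at most 20%, and gives benefit of methylprednisolone as the reason for stopping. A rate that low leaves no room for placebo to be more than 20 points lower, so condition and reason point in opposite directions.

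This rule decides whether the trial goes on. The same section says that no data safety monitoring board is required, so the written rule carries more weight than usual. Taken literally, it can never stop for the effect the trial was designed to find. The obvious repair, dropping the 20% ceiling, leaves a stop on a bare point estimate equal to the design effect, with the final test still at 0.05.

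**Working it through.** **Inputs.** From Sample size: control rates 87.5% and 67.5%, 67 per group before loss, 74 per arm, 148 in total. From Randomisation and blinding: 1:1 allocation. From Patient safety: look at 50%, thresholds of 20% and 45%. Interim size: 0.5 × 148 = 74 patients, 37 per arm (about 33 if 10% are lost).

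**1. The plan's own figure.** Two-sided 5%, 80% power, pooled variance, mean rate 0.775:

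n = [1.96 × √(2 × 0.775 × 0.225) + 0.842 × √(0.875 × 0.125 + 0.675 × 0.325)]² / 0.20² ≈ 67.3

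This is 68 when rounded up, against 67 stated; power at 67 per arm is 79.9%. The figure reproduces only with 20% as an absolute difference between proportions, which confirms the scale. The article gives no operating characteristic for the interim rule to reproduce.

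**2. Can the rule fire with methylprednisolone ahead?** Let M and P be the observed control rates. The rule needs M ≤ 20 and |M − P| > 20. If M > P, then P < M − 20 ≤ 0, which is impossible.

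In counts at 37 per arm: 20% of 37 is 7.4, so at most 7 methylprednisolone patients are controlled and the arms differ by at least 8.

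- Methylprednisolone ahead: 0 outcome pairs.
- Placebo ahead: for each m = 0 to 7, placebo can be m + 8 to 37, which is 30 − m values. The sum is 8 × 30 − 28 = 212 pairs.
- At 33 per arm: 0 and 168.

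**3. How often would it fire as written?** Exact binomial, 37 per arm:

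| True rates, methylprednisolone vs placebo | Probability |
|---|---|
| 87.5% vs 67.5% (design) | about 3 × 10⁻²¹ |
| 20% vs 67.5% | 53% |
| 10% vs 67.5% | 97% |

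The last two rows use illustrative methylprednisolone rates that are not in the article.

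**4. If the 20% ceiling is a slip.** Suppose a methylprednisolone lead above 20 points stops the trial, and otherwise a chi-square test at 0.05 is done at 74 per arm. Control is treated as a binary outcome, as a proxy for the planned analyses. With both arms at 67.5%:

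- Stop at the look in favour of methylprednisolone: 3.1%.
- Overall two-sided type I error: about 7.2%, so final rejections add 7.2 − 3.1 = 4.1 points.
- False claims of benefit: about 4.7%, against a nominal 2.5%.
- The final test alone: 5.0%.

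At the design rates, the chance of stopping at the look is about 49%, on 6-month data in a trial with 12 months of follow-up.

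**5. The 45% limit.** With a true placebo rate of 67.5%, the largest true benefit is 100 − 67.5 = 32.5 points. A placebo lead above 45 points needs methylprednisolone below 67.5 − 45 = 22.5%. Observed rates vary: at 37 per arm, a methylprednisolone lead above 45 points has probability 0.4% at the design rates.

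**The case against.** The strongest reply is that the clause is a plain slip in a condensed article and that interim error control commonly sits in the statistical analysis plan. The absence of a boundary in the article is indeed no finding by itself. But the article does state a termination rule, states it wrongly, and no other section repairs it. Nor does it show which words are the slip, so step 4 is conditional on a guess about intent.

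A relative reading of the 20% difference would let methylprednisolone lead, for example 20% against below 0.20/1.2 = 16.7%. The Sample size section does not support that reading, and a control rate of 20% or less would hardly be a convincing effect.

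Three stronger readings are tempting and do not hold:

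- **That the 45% limit cannot be reached.** It is worded without direction, so a placebo lead can exceed it, and chance can carry an observed methylprednisolone lead past it. It stands under Patient safety and may be a safety check.
- **That type I error is 9.3%.** That figure counts stops in either direction (6.2% at the look). The stated reason for stopping is an effect in the intervention arm, so the one-directional 7.2% fits better.
- **That the trial would declare benefit on data showing the drug to be worse.** The article says only that the study is terminated for that reason. It does not say that this replaces the final analysis.

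It is also fair that a chi-square test on binary control is not the planned primary analysis, so the error rates in step 4 are illustrative.

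**Conclusion.** Wrong as written. On the absolute scale of the Sample size section, the stop for a convincing effect of methylprednisolone can be met only with placebo more than 20 points ahead. This is arithmetic and holds at any sample size and for any true rates. The rule can never stop for the hypothesised benefit, and its stated reason is false if it fires.

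The error inflation is secondary. It assumes that the 20% ceiling is the slip, that only a methylprednisolone lead stops the trial, that control is binary, and that both arms are at 67.5%. It also takes the single 0.05 threshold to apply to the final test without adjustment for the look.

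On the 45% limit, the supportable point is narrow: under the assumed placebo rate it cannot work as an efficacy boundary, and its direction and consequence are not stated.

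**What to change.** Before the interim look, reconcile the stop condition with its stated reason:

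- Replace the clause that pairs a difference above 20% with a methylprednisolone rate of at most 20% by one directional statistical boundary on the named primary analysis that preserves the overall 5% error. Haybittle-Peto at p<0.001 with the final test at 0.05 is one option; on the same binary proxy it gives an overall error of 5.06%. O'Brien-Fleming bounds would also serve.
- State that a lead for placebo is not labelled as efficacy.
- Keep the 45% limit, but state its direction, its purpose and what follows if it is exceeded.

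The cost is protocol and analysis plan wording only. The downside is a lower chance of stopping early than under a rule of more than 20 points.

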### Data safety

The handling of personal data complies with the Dutch Personal Data Protection Act (AVG). All data collected for the trial, including but not limited to demographic data, audiological questionnaires and data from the DizzyQuest app will be entered in a ISO 9001 and ISO 27001:2005 certified Castor EDC database (electronic CRF). Data will be protected with a unique subject identification code which is linked to a password protected subject identification list. Only members of the study team, who will be documented on the site signature and delegation log per site, will have access to the study data. The sponsor and investigator will keep a clinical trial master file which will contain the essential documents relating to the clinical trial.

